## Abstract

**Background:**

Bedside lung ultrasonography has been widely used in neonatal intensive care units (NICUs). Lung ultrasound scores (LUS) may predict the need for pulmonary surfactant (PS) application. PS replacement therapy is the key intervention for managing moderate to severe neonatal respiratory distress syndrome (NRDS), with early PS administration playing a positive role in improving patient outcomes. Lung ultrasonography aids in the prompt diagnosis of NRDS, while LUS offers a semi-quantitative assessment of lung health. However, the specific methodologies for utilizing LUS in clinical practice remain controversial. This study hypothesizes that, in very preterm infants [<32 weeks gestational age (GA)] exhibiting respiratory distress symptoms, determining PS application through early postnatal LUS combined with clinical indicators, as opposed to relying solely on clinical signs and chest x-rays, can lead to more timely PS administration, reduce mechanical ventilation duration, improve patient outcomes, and lower the occurrence of bronchopulmonary dysplasia (BPD).

**Methods and design:**

This is a protocol for a prospective, non-blinded, randomized controlled trial that will be conducted in the NICU of a hospital in China. Eligible participants will include very preterm infants (< 32 weeks GA) exhibiting signs of respiratory distress. Infants will be randomly assigned in a 1:1 ratio to either the ultrasound or control group. In the ultrasonography group, the decision regarding PS administration will be based on a combination of lung ultrasonography and clinical manifestations, whereas in the control group, it will be determined solely by clinical signs and chest x-rays. The primary outcome measure will be the mechanical ventilation duration. Statistical analysis will employ independent sample *t*-tests with a significance level set at α = 0.05 and a power of 80%. The study requires 30 infants per group (in total 60 infants).

**Results:**

This study aims to demonstrate that determining PS application based on a combination of LUS and clinical indicators is superior to traditional approaches.

**Conclusions:**

This approach may enhance the accuracy of NRDS diagnosis and facilitate early prediction of PS requirements, thereby reducing the duration of mechanical ventilation. The findings of this research may contribute valuable insights into the use of LUS to guide PS administration.

## Background

1

Neonatal respiratory distress syndrome (NRDS), resulting from a deficiency in pulmonary surfactant (PS), stands as a primary cause of mortality among premature infants. Currently, clinical symptomatology, combined with chest x-rays, constitute the primary diagnostic modalities for NRDS. However, the subjective nature of symptom recognition and the limitations of chest x-rays, including poor sensitivity and specificity along with radiation exposure, pose challenges for clinicians in the early diagnosis of NRDS. In recent years, bedside lung ultrasonography has gained widespread utilization in neonatal intensive care unit (NICU) settings, with numerous studies showcasing its substantial advantages in NRDS diagnosis (1). Consequently, the latest guidelines have recommended the adjunctive use of bedside lung ultrasonography in NRDS diagnosis (2).

Continuous positive airway pressure ventilation and surfactant replacement therapy stand as key interventions for moderate to severe NRDS (3). Early administration of PS has demonstrated positive roles in reducing mortality, improving prognosis, shortening the duration of invasive ventilation, and mitigating the occurrence of bronchopulmonary dysplasia (BPD) among premature infants (4, 5). A study suggests that prophylactic PS administration within 30 min postpartum significantly diminishes the severity and incidence of respiratory distress syndrome (RDS), thereby reducing neonatal mortality and pneumothorax risks (6). Additionally, the 2022 Update of the European Consensus Guidelines on the Management of Respiratory Distress Syndrome strongly recommends early initiation of PS therapy in symptomatic patients with NRDS prior to clinical deterioration, advocating for less-invasive delivery methods (2). Nevertheless, in clinical practice, not all premature infants presenting with respiratory distress symptoms manifest NRDS. Transient RDS, neonatal pneumonia, and meconium aspiration syndrome can also precipitate early respiratory distress. Autopsy findings indicate misdiagnosis rates of NRDS as high as 57% in premature infants (7). For mild NRDS cases, relief through continuous positive airway pressure ventilation alone may suffice, obviating potential airway injury from PS administration. Prompt diagnosis of etiology and decision-making regarding PS administration in the early postnatal period poses a dilemma for clinicians. Current guidelines recommend early PS therapy when infants require respiratory support with positive end-expiratory pressure (PEEP) exceeding 6 cmH2O and fraction of inspired oxygen (FiO_2_) surpassing 0.3; however, there is no consensus on the criterion and cut-off to adopt for surfactant treatment (2, 8). However, patient FiO_2_ requirements vary vastly with postnatal time and respiratory support methods. Moreover, subjective symptom recognition and severity assessment lack objective criteria, further complicating the early decision-making process regarding PS application. On the one hand, waiting to fulfill FiO_2_ criteria for surfactant replacement therapy can lead to delayed administration and reduce the potential beneficial effects of the surfactant (9). On the other hand, loosening the criteria for medication use may result in excessive application of PS. Thus, balancing timely treatment initiation against the risk of overuse remains a challenge (10).

Lung ultrasound scores (LUS) provide a quantitative evaluation of lung ultrasound results.

Numerous studies have shown that LUS can assist in assessing the need for PS application in patients with NRDS. In a prospective study from 2018 involving 133 premature infants born at a gestational age (GA) of less than 30 weeks, it was confirmed that LUS correlated significantly with oxygen saturation and FiO_2_ during the early postnatal period. This correlation helps determine the respiratory status in infants’ and can predict the necessity for PS administration, with the likelihood of PS administration increasing from 51% to 82% or 92% when LUS are more than 6 out of 8 (11). Alternatively, LUS exhibited the highest predictive ability for the initial PS administration compared with FiO_2_ and Silverman scores (12). Additionally, retrospective studies have indicated that utilizing LUS to anticipate PS administration can reduce the misdiagnosis rate of RDS and subsequently lower PS usage by 30.1% (13). Furthermore, LUS offer significant advantages in promptly determining the need for PS application in infants and facilitating early PS administration, within 3 h postnatally. Research has shown that LUS can shorten the durations of both invasive and non-invasive ventilation, thereby reducing the incidence of subsequent BPD (14).

In existing studies, the utilization of LUS to assess NRDS often involves simplified adaptations from adult LUS systems. A unified standard for LUS assessment in neonates remains elusive (14, 15). Variations exist in the scoring locations and methods of LUS applied across different studies. Furthermore, a consensus on the threshold of LUS for PS application has yet to be established, hindering its widespread clinical application. Therefore, this study aimed to demonstrate, through a randomized controlled trial, that for very preterm infants (< 32 weeks GA) experiencing respiratory distress, determining PS application based on LUS combined with clinical indications can lead to more accurate NRDS diagnosis compared with traditional methods that rely on clinical indications and chest x-rays. Hence, this approach may facilitate the early and appropriate use of PS, within 3 h postnatally, thereby reducing mechanical ventilation duration, improving patient outcomes, lowering the incidence of BPD, and decreasing medical expenses. Furthermore, lung ultrasonography can partially substitute for chest x-rays in the diagnosis of early NRDS, significantly reducing early radiation exposure for patients.

## Methods

2

### Study design

2.1

This prospective, non-blinded, randomized controlled trial is to be conducted in the NICU of a tertiary referral hospital in China. This NICU serves as the regional referral center for high-risk newborns and pregnant women, with an annual delivery volume exceeding 6,000, including approximately 200 very preterm infants (< 32 weeks GA). This study primarily targeted very preterm infants presenting with symptoms of respiratory distress. Following enrollment, participants will undergo standardized trial procedures (Figure 1).

**Figure 1 F1:**
[figure not shown]
Fowchart of participant selection and treatment.

All very preterm infants will undergo antenatal consultations before birth. Neonatologists will engage in thorough discussions with the parents of premature infants, informing them about the risks associated with premature birth at this GA and outlining the treatment process post-birth. Before delivery, a neonatal resuscitation team comprising neonatal and obstetric specialists will be established. Following delivery, premature infants will be transferred within the hospital using transport incubators, and a T-piece resuscitator will be utilized during the transfer process. Within 1 h after birth, all enrolled infants will undergo lung ultrasonography, and those meeting the diagnostic criteria will receive PS as per the trial protocol. Subsequently, they will undergo regular lung ultrasound monitoring until discharge or at 36 weeks corrected age (CA).

Centers participating in the study routinely use lung ultrasonography. Two ultrasound physicians and five neonatologists will participate in this study. Both ultrasound physicians have received comprehensive training in lung ultrasonography and LUS application. Lung ultrasonography will be performed by two ultrasound physicians, who each have more than 2 years of experience in neonatal lung ultrasound and have received systematic training before the study, including study protocols, lung ultrasound scoring, and interpretation of lung ultrasound images. In order to ensure the consistency of scoring results, the two doctors will respectively determine the LUS based on ultrasound images. If the scores are consistent, the results will be recorded. If the score difference is ≥2, the final score will be determined by the two doctors after discussion.

Other research personnel have completed standardized training, including familiarization with the trial protocol, methods of recording case records, and criteria for assessing complications.

Lung ultrasonography will be conducted using the Mindray M9 ultrasound system equipped with a linear, high frequency (10–15 MHz) transducer.

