### Blinding

2.5

In this study, as the administration of the first dose of PS depends on the initial lung ultrasound results, ultrasound physicians and neonatologists will be informed of the infant's group assignment at the beginning. However, subsequent ultrasound results after the first dose will not be disclosed to the clinical team to prevent any influence on the assessment of indications for the second dose of PS. In addition, blinding will be implemented for the members involved in outcome assessment and data analysis to reduce bias.

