### Assessment points

2.6

The main assessment and recording of the infants’ indicators will occur at the following time points (Table 1).

**Table 1 T1:** Neonatal assessment chart.

Measure	Assessment point							
	Allocation within 1 h after birth	4–10 h after PS	24 h	3 days	7 days	14 days	28 days	36 weeks CA/discharge
LUS	×	×	×	×	×	×	×	×
Clinical index								
Silverman Anderson score	×	×	×	×	×	×	×	×
Respiratory support mode	×	×	×	×	×	×	×	×
Ventilator parameters	×	×	×	×	×	×	×	×
Medication use of PS	×		×					
Outcomes assessment								
NIV (hours)								×
IMV (hours)								×
Supplemental oxygen (days)								×
PS (%)								×
Early PS (%)								×
Birth to the application of 1st PS (min)								×
LOS								×
Costs associated with hospital care								×
Complications								
hsPDA (%)								×
BPD (%)								×
IVH (%)								×
NEC stage I or II (%)								×
ROP (%)								×

NIV, non-invasive ventilation; IMV, invasive mechanical ventilation; Early PS, pulmonary surfactant administered within 3 h after birth; LOS, length of stay; hsPDA, hemodynamically significant patent ductus arteriosus; IVH, intraventricular hemorrhages; BPD, bronchopulmonary dysplasia; NEC, necrotizing enterocolitis; ROP, retinopathy of prematurity.

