#### Ultrasound group

2.7.1

Lung ultrasonography will be performed within 1 h of admission, followed by lung ultrasound scoring (refer to Figure 2 for the segmentation and scoring methods). In the case of different score patterns in the same area, the worst will be selected. If the lung ultrasound confirms RDS and LUS is more than 8, a full dose of PS will be promptly administered at 200 mg/kg (Poractant Alfa, Curosurf®). If the lung ultrasound does not indicate RDS or if LUS is 8 or less, clinical monitoring will continue. Should the clinical criteria for NRDS be met, a full dose of PS will be administered at 200 mg/kg (Poractant Alfa, Curosurf®). In terms of the administration method, less-invasive surfactant administration (LISA) will be employed for infants in a non-invasive ventilation state, while those in an invasive ventilation state will receive PS via endotracheal tube. Lung ultrasound and scoring will be repeated 4–10 h post the first PS dose administration (with scoring results withheld from the clinical team). Repeated PS administration will occur if the criteria are met, with lung ultrasound scoring conducted prior to each administration (with scoring results withheld from the clinical team). Repeated PS administration will be completed via endotracheal tube.

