#### Control group

2.7.2

In cases where clinical diagnosis confirms NRDS, PS will be administered at a dosage of 200 mg/kg (Poractant Alfa, Curosurf®). LISA will be employed for infants in a non-invasive ventilation state, while those in an invasive ventilation state will receive PS via endotracheal tube. If clinical manifestations do not meet the diagnosis of NRDS, PS will not be administered.

All enrolled infants will undergo lung ultrasound scoring at 24 h, 3 days, 7 days, 14 days, 28 days, and 36 weeks CA (prior to discharge) (with scoring results withheld from the clinical team).

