### Data collection and diagnoses

2.10

Patient demographic data mainly include: (1) GA, birth weight, singleton or multiple births, sex, prenatal steroid use, mode of delivery, presence of intrauterine distress, and maternal pregnancy complications; and (2) Apgar scores at 1 min, 5 min, and 10 min, as well as umbilical cord blood gas analysis.

Clinical information at each time point (at admission, 1 h after birth, 4–10 h after PS administration, 24 h, 72 h, 7 days, 14 days, 28 days, and before discharge or at 36 weeks CA) include (1) timing, dosage, and method of the initial PS administration; (2) SAS, respiratory machine mode, oxygen saturation index, and FiO_2_ levels at each time point; and (3) LUS at each time point. LUS will collect individual scores for each lung field as well as the total score.

Complications and outcomes: (1) Respiratory complications: this includes the occurrences of infectious pneumonia, pneumothorax, pulmonary hemorrhage, and BPD, along with their severity grading; (2) Cardiovascular complications: specifically, hemodynamically significant patent ductus arteriosus (hsPDA); (3) Other complications in premature infants: these encompass IVH, periventricular leukomalacia, NEC, late-onset sepsis, ROP, intrauterine growth restriction, and more; and (4) Length of hospital stay and associated costs.

BPD diagnosis will adhere to the 2018 National Institute of Child Health and Human Development (NICHD) classification. Diagnosis of hsPDA will rely on clinical signs and echocardiography (20). IVH and white matter injury will be diagnosed via cranial ultrasound, with IVH graded using the Papile classification (21). NEC staging will follow modified Bell criteria (22). ROP diagnosis and staging will be based on fundoscopic examinations conducted by ophthalmologists.

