Based on prior research, this study protocol has been refined and improved in the following aspects: (1) Patient selection: very preterm infants with a GA of less than 32 weeks will be selected. According to previous study reports, the incidence of NRDS increases gradually with a decrease in GA. The incidence of NRDS in extremely preterm infants (GA ≤28 w) has been reported to be 93%; however, even among late preterm infants at 34 weeks GA, 10.5% of patients were diagnosed with NRDS (29, 30). In preterm infants below 32 weeks GA, early postnatal respiratory distress can be caused by a variety of causes. Differential diagnosis through traditional imaging is not only less sensitive but also brings about the challenges of radiation exposure. Patients often have delayed application or overuse of PS owing to misdiagnosis. Our study will include this population as the research object, hoping to identify NRDS more accurately and guide PS application through non-invasive methods in the early stage. (2) The clinical application of LUS was optimized: most previous studies judge whether to use PS only according to LUS, ignoring the possibility that other diseases causing respiratory distress may be misdiagnosed as NRDS. The severity of lung lesions caused by different diseases cannot be compared in parallel by LUS. In our study, the researchers first diagnosed NRDS through lung ultrasound and then assessed the severity of NRDS according to LUS and guided the application of PS. The combination of qualitative diagnosis and semi-quantitative assessment was more reasonable. In the diagnosis of NRDS by pulmonary ultrasound, the lesions may appear in any lung field; the pulmonary ultrasound guidelines clearly indicate that the lung lesions of NRDS mainly appear posteriorly, and therefore, the examination of the posterior region should not be ignored (19). In previous studies, in order to avoid moving patients, only the anterior and lateral lung fields were examined and scored, which may affect the accuracy of results (25, 31). In our study, according to the pulmonary ultrasound guidelines for lung partitioning, the anterior, lateral and posterior lungs were comprehensively evaluated and the scores of each lung field were recorded; the final total score was then calculated, which will be more accurate than the calculations in previous studies. (3) Timing of lung ultrasonography: previous studies have limited time points for lung ultrasound assessments, usually within the first 24 h post-birth. However, in the early postnatal period, premature infants experience rapid changes in their conditions and may require repeated administration of PS. Therefore, in our study design, the ultrasound group will undergo multiple lung ultrasound examinations within the first hour after birth, 4–10 h after the initial PS administration, prior to subsequent PS administration, and at 24- and 72-h post-birth. This will be the highest frequency of lung ultrasound examinations among known studies of the same type, and this approach allows for better monitoring of early postnatal lung ultrasound dynamics. Additionally, follow-up lung ultrasonography will be conducted at 1, 2, and 4 weeks after birth, as well as before discharge, thereby providing a basis for prognostic assessment; (4) Treatment method: following the 2022 European Consensus Guidelines on the Management of Respiratory Distress Syndrome, NCPAP combined with LISA was identified as the preferred treatment for preterm infants with spontaneous breathing after birth (2). Therefore, in this study, for infants receiving non-invasive ventilation (NCPAP or NIPPV) and exhibiting spontaneous breathing, priority will be given to the LISA method to reduce the risk of airway injury. This study aims to combine non-invasive diagnosis methods with non-invasive treatment to reduce the requirement for early invasive operations after the birth of preterm infants.

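### No stated rule withholds a control infant's first-hour lung ultrasound from the unblinded neonatologists who decide on surfactant

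*Protocol article*

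**What the plan says.** Three places schedule the first-hour scan without regard to arm.

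- Section 2.1: "Within 1 h after birth, all enrolled infants will undergo lung ultrasonography". The same sentence goes on to say that infants who meet the diagnostic criteria receive surfactant, without saying which criteria apply in which arm.
- Table 1 marks LUS in the column headed "Allocation within 1 h after birth".
- Section 2.10 includes LUS among the data under "Clinical information at each time point (at admission, 1 h after birth" and later visits.

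Three other places are less clear about controls.

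- Section 2.7.1, on the ultrasound group: "Lung ultrasonography will be performed within 1 h of admission, followed by lung ultrasound scoring".
- Section 2.7.2, on the control group, lists scans from one day of age: "All enrolled infants will undergo lung ultrasound scoring at 24 h, 3 days, 7 days, 14 days, 28 days, and 36 weeks CA".
- The Discussion, on timing of scans: "the ultrasound group will undergo multiple lung ultrasound examinations within the first hour after birth".

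On disclosure, section 2.5 tells the ultrasound physicians and the neonatologists the allocation, "as the administration of the first dose of PS depends on the initial lung ultrasound results". It then states that "subsequent ultrasound results after the first dose will not be disclosed to the clinical team", so that the decision on a second dose is not influenced. Limitation (1) in the Discussion repeats the non-disclosure rule but leaves the first scan out of it, and does not restrict that exception to one arm.

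**The concern.** The first-hour ultrasound and its score are the information that this trial randomises. Ultrasound-arm clinicians act on it; control-arm clinicians are meant to decide on clinical signs and chest radiography. If the control infant is scanned too and the result is open to the treating team, the separation between the arms rests only on the clinicians setting aside what they have seen.

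The control criteria in section 2.8 are partly numeric (oxygen saturation, FiO2) and partly observer-rated (worsening symptoms, Silverman Anderson Score). A neonatologist who has seen a high LUS might read the rated items as worse or reassess sooner, and so give surfactant earlier. One who has seen a low LUS might wait. Either could affect the use and timing of surfactant, which are secondary outcomes, and through them the duration of ventilation, the primary outcome.

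The protocol already accepts this reasoning for the second dose, where it withholds later scans. The first dose in the control arm is the decision under test, and there the safeguard is not written.

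**Working it through.** No arithmetic applies. The check is to take one scan, a control infant's first-hour scan, and see which statements reach it.

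**Step 1: is the scan planned?** Section 2.1, Table 1 and section 2.10 agree that it is. No statement says that controls are not scanned in the first hour. The other three places do not settle the matter:

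- Section 2.7.1 describes the scan where it drives treatment. That does not exclude one in controls.
- The list in section 2.7.2 covers all enrolled infants, so it leaves out the first-hour scan for the ultrasound group as well, which certainly has one. It reads as a follow-up schedule.
- The Discussion sentence also credits the ultrasound group with the 24 h and 72 h scans, which section 2.7.2 gives to everyone. It is therefore not exclusive.

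The most natural reading is that all infants are scanned and only the ultrasound arm acts on the result. Sections 2.7.1 and 2.7.2 do not say so plainly.

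**Step 2: does any withholding rule reach it?**

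| Statement | What it withholds | Reaches a control's first-hour scan? |
|---|---|---|
| 2.5 Blinding | Results after the first dose | No. The scan can come before any dose, and a control who never receives surfactant has no first dose |
| 2.7.1 Ultrasound group | The scan 4–10 h after the first dose, and those before repeat doses | No. Other arm, later scans |
| 2.7.2 Control group | Scans from 24 h onward | No. Starts too late |
| Discussion, limitation (1) | All but the first scan | No. Exempts it, in either arm |

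None of the four reaches it.

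**Step 3: does the reason for disclosure apply?** Section 2.5 opens the first scan because the first dose depends on it. Under section 2.7.1 that is true in the ultrasound group (RDS on ultrasound with LUS above 8). Under section 2.7.2 the control dose depends on the clinical diagnosis alone, so the reason has no force there.

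**Step 4: is there room for influence?** Section 2.8 requires progressive symptoms together with saturation of 85% or less, a Silverman Anderson Score above 5, or an hourly rise in that score of more than 2 with FiO2 above 0.4 (above 0.3 below 28 weeks). The symptoms and the score are rated at the bedside by staff who know the allocation. There is some room, bounded by the numeric items.

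**The case against.** The strongest reply is that the control decision is already fenced in. The Abstract bases it on clinical signs and chest radiography alone, section 2.7.2 forbids surfactant when the clinical picture does not meet the diagnosis, and section 2.8 gives thresholds. A high LUS by itself could not lead to surfactant in a control without a breach of protocol. This stands as a limit on the size of the problem. It does not close the gap, because these rules govern what the decision rests on and not what the clinician has seen, and part of the criteria is judged.

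A second reply is that a condensed article may leave to the full protocol who sees which result, and that the stated reason for disclosure implies it was meant for the ultrasound arm only. The intention can indeed be inferred. But the article does set disclosure rules, scan by scan, and limitation (1) states the exception without restricting it to an arm. Read literally, it opens the control result.

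A reader might also infer that the protocol contradicts itself on whether controls are scanned. The text does not support that: the places set against section 2.1 are silent or non-exclusive. Figure 1 is not shown and may state the intention directly.

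**Conclusion.** The point holds as a gap in the disclosure rules. If controls are scanned in the first hour, as section 2.1, Table 1 and section 2.10 indicate, no stated rule keeps the result from the unblinded neonatologists before they decide on a control infant's first dose. It should be fixed, because it touches the contrast under test and costs little to close.

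Its size is unknown. The document gives no rate at which control decisions might follow a visible score, and the direction is not assured: high scores could bring surfactant forward and narrow the difference between arms, while low scores could delay it and widen the difference. A reader might infer a definite dilution of the effect or a definite loss of power. Any such figure would rest wholly on an assumed share and an assumed direction, so none is given.

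The conclusion rests on two assumptions: that the all-infant schedule is the intended one, and that no rule outside the article already withholds the control result.

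**What to change.** Keep the first-hour scan in both arms and change the wording as follows.

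1. In 2.5 and limitation (1), restrict disclosure of the first scan to the ultrasound group.
2. In 2.7.2, state that control infants have the first-hour scan, and that its images and score are withheld from the treating team, except for a finding that needs urgent care, such as pneumothorax.
3. In 2.1, make the surfactant sentence arm-specific: RDS confirmed on ultrasound with LUS above 8, or the clinical criteria, in the ultrasound group; the clinical criteria only in the control group.

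The scan at 4–10 h after surfactant needs no new rule, since 2.5 already covers it.

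The cost is wording in four places and one more withheld scan per control infant, with no added patients or visits. Section 2.1 has the scans done and scored by two ultrasound physicians, and results are already withheld for later scans, so the routine exists. Dropping the control scan would also close the gap, but it is not an equal alternative. No listed outcome would be lost, since secondary outcome (4) names LUS only from 3 days. The control arm would, however, lose its only first-hour LUS, and with it the baseline comparison of severity and the starting point for the later scores.
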